### Outcomes measures

#### Primary outcome measure

Misbeliefs and attitudes of HP.○ HC-PAIRS. This self-administered questionnaire was designed to assess attitudes and beliefs of PC physicians on NCLBP. Domenech et al. [44] validated into Spanish the original English version in 2013. After the cross-cultural adaptation, the Spanish version of HC-PAIRS proved to be a reliable, valid and sensitive instrument. The questionnaire consists of 15 statements that suggest a direct link between pain, functional limitation and disability [44]. Each statement is followed by a 7 point Likert scale (1 = strongly disagree, 4 = neither agree nor disagree and 7 = strongly agree). The total score ranges from 1 to 105. Higher scores indicate strong fear-avoidance beliefs on the link between chronic pain and disability [44].

#### Secondary outcome measures

Fear-avoidance beliefs of HP.○ Fear Avoidance Beliefs Questionnaire (FABQ). This self-administered questionnaire was developed to measure the beliefs and attitudes of fear-avoidance in patients with LBP on physical and / or occupational activities [45]. The questionnaire is divided into two subscales: FABQ-physical activity and FABQ-work. It consists of 16 sentences on the relationship between pain and physical activity (first 5 items) and work (last 11 items). Each statement is followed by a 6 point Likert scale (0 = strongly disagree and 6 = strongly agree). For both subscales high scores indicate strong fear-avoidance beliefs [45]. This questionnaire has been validated in Spanish. The Spanish version of the FABQ has good internal consistency and reliability. Although it was created to assess fear-avoidance beliefs of patients, this questionnaire has also been used to measure the beliefs of general practitioners and rheumatologists [44, 45].Knowledge about NPP.○ NPP questionnaire. This self-administered questionnaire was developed by Lorimer Moseley in 2003 [46] to assess how an individual conceptualizes pain. An acceptable internal consistency and good test-retest reliability was demonstrated [47]. The original English version was translated into Spanish by the Language Service of the Rovira and Virgili University [48]. The questionnaire consists of 19 statements that refer to the origin and meaning of pain with three possible answers: true, false or doubtful. Each correct answer is scored with 1 point, while incorrect, doubtful or unanswered responses are scored with 0 points [47]. Due to the fact that the questionnaire was designed for patients or HP, the present study omitted the colloquial terms shown in parentheses, using only the terms intended for HP [48].Other variables○ Sociodemographic variables: sex, age, descendency, health discipline and specific training in the vertebral spine.○ History of LBP.○ Acceptability and satisfaction of HP about the intervention.○ Number of consultations to the web site.○ Number of video views by each participant.

### Web site development and educational material

Once all the information in the QUAL phase has been analyzed and before the QUAN phase begins, the web site and the educational material will be developed. The results of the QUAL phase will be the starting point for the completion of the connection phase, where the educational materials will be developed. The themes and sub-themes that emerge from the QUAL phase will form the basis of the content of the educational material using the NPP. Therefore, the objective of this phase is to respond to the misconceptions about the origin and meaning of pain identified in the QUAL phase using the NPP.

The web site will be created using Drupal content management system. An external researcher from the Higher Polytechnic School of the University of Lleida will take part in this phase. The platform will be built based on the creation of game-based learning scenarios. The application of the elements of games in non-play contexts is called gamification [49, 50]. Its use will provide an innovative and attractive design where HP will be able to work the cognitive processes in a more creative way, thus favoring learning. In addition, it will allow HP to deal with real problems related to the approach of patients who suffer from NCLBP in PC, thus producing changes in their behavior from the stimulus of their motivation [49–53].

The educational material will be presented in different formats, such as explanatory videos and 3D graphic representations, using the chronic NPP. In addition, the authors will use frequent clinical questions about NCLBP patients. Furthermore, HP will be able to contact a chronic pain specialist via email or videoconference [16]. All the videos will be elaborated with the support of the Superior Polytechnic School of the University of Lleida.

### Educational intervention

Intervention group: This group will have access to our web site where they will find information related to NCLBP. This information will be presented using dynamic explanatory 3D videos. The aim of this intervention is to change and modify misbeliefs and attitudes about NCLBP of physicians and nurses working in PC settings, using a web-based educational tool with the additional result of increasing knowledge on NPP and reducing fear-avoidance beliefs.Control group: This group will have access to a video where a group of primary health care professionals explain the content of the CPG for low back spine pathology in adults. This group will also have access to the complete CPG in PDF format.

### Data collection

QUAL: In order to respond to the QUAL objective of this study, the authors will use semi-structured individual interviews. The first author will be responsible for conducting the interviews. Before the interview, participants will be asked to complete a personal data form for statistical purposes. Interviews will be conducted in Spanish or Catalan (depending on the subject’s mother tongue) and will be recorded in audio with the HP previous consent. In order to promote greater participation, the interviews will be carried out during the participants’ working hours, in authorized spaces within the PC settings, provided by the reference person of the corresponding PC center. The interviewer will have two interview guides, one for the medical staff (see Additional file 1) and one for the nursing personnel (see Additional file 2) built on the knowledge gained from the scientific evidence and the research group’s experience. The questions will be presented in an open format and will be adapted to the HP to which they are addressed. The interviews are meant to last about an hour.QUAN: The intervention will last for 2 weeks, and variables will be measured pre- and post-test. The authors based the duration of the intervention on Valenzuela et al. [16] and Keulers et al. [54] studies, because of the similarities in design and characteristics. An external researcher from the Polytechnic University of Lleida will be responsible of encrypting and storing all the data from this study, avoiding any information bias, as well as the maintenance of the web site.The first author of this study will meet the study subjects to inform them about the study and deliver the informed consent. Once individuals have signed the consent form, they will be given a password to access the web site. After logging in to the website, HP will need to fill out a personal data form for statistical purposes and will be asked to complete the questionnaires. Once this step has been completed, subjects will see a message on the screen to participate in the control or the intervention group. The control group will be provided a link to have access to an explanatory video based on the CPG for LBP, as well as to the full text of the CPG in PDF format. The intervention group will have access to (will be provided with a personal password) the educational web site from any computer or laptop and at any time, until the end of the trial.Both groups will receive two emails during the study (one two days before the end of the study and the second on the last day) to remind them to complete the questionnaires. Once they complete this last step, they will end their participation in the study and will not longer have access to the web site.

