The study published by Darlow et al. [15] justifies the use of educational interventions to change the cognitive factors of HP involved in the treatment of NCLBP patients [15]. Several public health interventions have shown that HP’ re-education is effective in changing their cognition towards NCLBP and, consequently, changing their misbeliefs and attitudes towards treatment that may be reflected in those patients [20, 21]. The Societal Impact of Pain [22], a platform supported by the European Federation of IASP Chapters, urges governments and health institutions in the European Union to enhance education in knowledge, prevention, diagnosis and treatment of pain among HP. At present, HP who work in PC centers have clinical practice guidelines (CPG) in order to transfer knowledge to specific recommendations, assisting them in making individual clinical decisions and unifying therapeutic criteria, with the aim of promoting higher quality and welfare equity [23–26]. In Spain, the effectiveness of CPG in PC to change clinical practice is moderated [24]. In 2004, the Catalan Health Institute promoted a CPG for low back spine pathology in adults [27]. These guidelines include teaching material and advice for patients. However, they lack a neurophysiological explanation of the procedures involved in pain [27]. In their systematic review and meta-analysis, Clarke et al. [28] suggest pain neurophysiology (NPP) as a promising educational strategy towards pain and physical, social, and psychological function in patients suffering from NCLBP. It has also been shown to have positive effects on pain perception, disability and catastrophism in patients with chronic conditions [29, 30]. This educational strategy is based on the description of the central and peripheral processing mechanisms of the nociceptive signal and the explanation of how this transmission is modulated by brain processing and influenced by psychosocial factors [16, 31]. The results obtained so far suggest that an educational intervention based on NPP can help HP to conceptualize pain and to modify attitudes towards the treatment of chronic pain in PC [32].

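### Web-site content is not closed before the post-test, so the pain-neurophysiology knowledge score can mix look-up with acquired knowledge, with a possible bias toward the intervention

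*Protocol article*

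**What the plan says.** The order of events is in Data collection (quantitative phase). After logging in, participants fill in a personal data form and the baseline questionnaires. Only then is the arm revealed: "Once this step has been completed, subjects will see a message on the screen to participate in the control or the intervention group". The intervention lasts 2 weeks. During it the intervention group may use "the educational web site from any computer or laptop and at any time, until the end of the trial". Both arms receive two emailed reminders to complete the questionnaires, "one two days before the end of the study and the second on the last day". On what follows completion, the article says: "Once they complete this last step, they will end their participation in the study and will not longer have access to the web site".

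On the content of the two arms:
- **Intervention.** Under Web site development and educational material, the themes from the qualitative phase "will form the basis of the content of the educational material using the NPP". The stated aim of that phase is to answer misconceptions about where pain comes from and what it means.
- **Control.** Under Educational intervention, this arm receives a video on the low back guideline, and "This group will also have access to the complete CPG in PDF format". Of the Catalan guideline for low back spine pathology in adults, the Background says: "However, they lack a neurophysiological explanation of the procedures involved in pain [27".

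The knowledge outcome is the NPP questionnaire, with 19 statements answered true, false or doubtful. Secondary outcome measures gives the scoring: "Each correct answer is scored with 1 point, while incorrect, doubtful or unanswered responses are scored with 0 points". Objectives names knowledge of pain neurophysiology as the secondary outcome.

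**The concern.** A knowledge test measures what a person has learned only if the teaching material is out of reach while it is taken. Here the material is out of reach at the pre-test, and nothing described puts it out of reach at the post-test. Part of a pre-post gain in the intervention arm could come from that change in conditions.

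The exposure is uneven between arms. The intervention content and the NPP questionnaire share a subject; the control material is said to lack it. Any look-up in the study's own material would therefore tend to favour the intervention. Randomisation does not balance this, because it arises after allocation.

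Look-up is plausible. Participants are not blinded, they have seen the items at baseline, and a doubtful answer scores 0, so each fact confirmed is worth a point.

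At stake is the interpretation of the secondary objective and, through it, the second hypothesis in the Background, which expects misbeliefs to fall as a result of a change in knowledge. If the NPP score is part look-up, that step cannot be read cleanly.

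**Working it through.** **1. Conditions at the two measurements (Data collection).**

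| | Pre-test | Post-test |
|---|---|---|
| Arm known to participant | No, shown afterwards | Yes |
| Educational content already opened to participant | No | Yes |
| Closing of content before the questionnaires | Not needed | None described |
| Site access ends | – | After completion |

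**2. What each arm can consult at the post-test.** Intervention: a site built on pain neurophysiology. Control: guideline video and PDF. The control guideline and the guideline described in the Background carry the same title, so I take them to be the same document. On that reading only the intervention arm's study material covers the tested subject.

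**3. The plan's own figure.** The only sample size is for HC-PAIRS: SD 9, difference 4.5, two-sided alpha 0.05, power 80%.

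n per group = 2 × (1.960 + 0.842)² × (9 / 4.5)² = 2 × 7.85 × 4 = 62.8, rounded up to 63.

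This reproduces the stated 63 (power 80.1% by the normal approximation). Nothing is sized on the NPP score, so this figure does not bear on the point.

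**4. Illustrative size.** The article gives no look-up rate, no number of items gained and no SD for the NPP score. All three are assumed here. Let f be the share of the intervention arm that looks up answers, k the items each gains, and s the SD of the score. Assume no true difference in retained knowledge and no look-up in the control arm.

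Shift in the mean difference = f × k:
- lowest: 0.10 × 1 = 0.1 points
- middle: 0.25 × 2 = 0.5 points
- highest: 0.50 × 4 = 2.0 points of 19

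With 63 per group, SE = √{[s² + s² + f(1 − f)k²] / 63}. The chance of a significant two-sided 5% result is P(|Z + shift/SE| > 1.96):

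| s | f | k | Shift | SE | Chance of p < 0.05 |
|---|---|---|---|---|---|
| 4 | 0.10 | 1 | 0.1 | √(32.09/63) = 0.714 | 5.2% |
| 3 | 0.25 | 2 | 0.5 | √(18.75/63) = 0.546 | 15.0% |
| 2 | 0.50 | 4 | 2.0 | √(12/63) = 0.436 | 99.6% |

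The range runs from almost no effect to near-certain significance. The arithmetic shows that the bias could matter, not that it does.

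**5. Reach.** HC-PAIRS and FABQ are agreement scales with no correct answer, so there is nothing to look up. The argument stops at the NPP questionnaire.

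**The case against.** The strongest reply is that the sentence on access may only describe closing the account. Participants log in to the web site to complete the baseline questionnaires, and the post-test appears to work the same way, so login has to stay open until submission. The article does not say that videos can be viewed while the questionnaire is on screen. The platform already sequences its steps at baseline, and page locking is the kind of detail a condensed article may omit. The words on any computer and any time describe access to the educational site, not where the post-test is taken. All of this is fair. It rules out saying that the test is in fact taken open-book or that the difference is in fact inflated. What remains is that the article does describe when access ends, places it after the questionnaires, and grants the intervention arm access until the end of the trial.

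A reader might also infer that the site contains the answers to the 19 items. The documents do not show this. The content depends on a qualitative phase still to be done, and overlap is inferred from the shared subject. Videos and game-based scenarios are also awkward to search during a test.

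Third, controls could consult outside sources, so zero look-up in that arm is an assumption. This weakens any claim that the error can run only one way, but not the imbalance in the material that the trial itself supplies.

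Finally, a reader might extend the point to the primary outcome. Recent exposure may colour answers to HC-PAIRS or FABQ, but that is a different matter from looking up answers, and the documents give no basis for sizing it.

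**Conclusion.** The point holds as a risk to one secondary outcome. The stated sequence leaves pain-neurophysiology material available to the intervention arm during the NPP post-test, while the control material is described as lacking that content. The NPP difference can therefore mix look-up with acquired knowledge, and the likely direction favours the intervention.

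The size cannot be determined from the document. The illustration of 0.1 to 2.0 points rests wholly on the assumed look-up shares and item gains; the chances of significance rest also on an assumed SD of 2 to 4 points and on no look-up among controls. The conclusion itself rests on two readings: that the post-test is completed without supervision, since none is described, and that the site's content overlaps with the questionnaire's subject. The primary analysis and the sample size stand. The change is worth making because it is cheap and protects the stated secondary objective.

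**What to change.** Amend Data collection so that, in both arms, the platform locks the educational content when the participant opens the post-test and keeps it locked until submission. Require the NPP questionnaire to be completed in one sitting, so that a participant cannot read the items, leave to consult the site and return. Content may be reopened after submission. If such a lock already exists, stating it settles the matter.

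The cost is a minor platform setting and a sentence or two of protocol text. The lock is not complete: outside sources remain available to both arms and a downloaded guideline PDF cannot be withdrawn. It does remove the imbalance created by the trial's own web site.

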
### Data analysis

QUAL: Before beginning the analysis, the interviews will be transcribed verbatim and reviewed by the authors. Deductive and inductive (free or emerging) coding will be used for data identification and integration, resulting in different meaning categories. Different conceptual themes will be generated through which the educational material will be built for the QUAN phase. The first author of the study will analyze the interviews and a different researcher will participate in the information triangulation to ensure the validity and reliability of the material [55, 56]. Subsequently, all the authors will participate in the data interpretation phase and the educational tool development. The Atlas.ti software will be used for the coding process and the information handling.QUAN: For statistical purposes the authors will use the SPSS software. For the descriptive analysis, continuous variables will be expressed with the mean and the standard deviation if their distribution is normal, or with the median and the interquartile range, if they do not follow this distribution. Absolute and relative frequency will be used for categorical variables. The t-Student test will be used for the comparison between the continuous variables and the Chi square distribution for the categorical variables. A non-parametric test will be used for the bivariate analysis if a normal distribution cannot be assumed. An alpha error of 0.05 (5%) will be assumed in the statistical inference.

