### Sample size

QUAL: The sample size will be determined by a convenience sampling method to achieve a representative number of HP. To ensure the discursive significance of the study results, the sample will be heterogeneous including doctors and nurses of different genders and age groups. The “snowball” strategy will be used to broaden the interviewed subjects. The final number of subjects will depend on the saturation of the information [37].QUAN: The sample size measurement is based on the study published by Domenech et al. [38] where the results obtained from the Health Care Providers Pain and Impairment Relationship Scale (HC-PAIRS) have been used as reference. Taking into account this study and other similar studies performed in general practitioners and physiotherapists [39–42], a standard deviation of 9 will be considered for the calculation of statistical power. A variation in the HC-PAIRS score of 4.5 (half the standard deviation) will be considered clinically significant. Accepting an alpha risk of 0.05 and a statistical power of 80% to reject the null hypothesis, using a bilateral test, the minimum number of participants will be 63 HP in each group. We assume that the dropout rate in the study will be 20%.

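### The only parametric test named for the pre/post outcomes is an unadjusted t test; adjusting for the baseline score is free and at least as precise in large samples

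*Protocol article*

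**What the plan says.** The Data collection section fixes two measurement times: "The intervention will last for 2 weeks, and variables will be measured pre- and post-test". Participants complete the questionnaires on the web site before they are shown their group, so a true pre-randomisation-message baseline exists for everyone who starts.

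The Data analysis section then gives one sentence on parametric comparisons: "The t-Student test will be used for the comparison between the continuous variables and the Chi square distribution for the categorical variables". A non-parametric test, described as bivariate, is the fallback if normality fails. No covariate, regression or ANCOVA is named, and nothing says whether the t test is applied to post-test scores or to pre-post differences.

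The Sample size section sets the target: "A variation in the HC-PAIRS score of 4.5 (half the standard deviation) will be considered clinically significant", with "a standard deviation of 9 will be considered for the calculation of statistical power". It does not say whether that SD belongs to scores or to changes. With "Accepting an alpha risk of 0.05 and a statistical power of 80% to reject the null hypothesis, using a bilateral test", it concludes that "the minimum number of participants will be 63 HP in each group", and then assumes 20% dropout without giving an enlarged number. The Randomization section specifies simple randomisation, with no stratification.

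**The concern.** In a randomised trial with the same questionnaire completed twice, two weeks apart, the baseline score is likely to be the most useful covariate available, and it costs nothing further to collect. The stated test does not use it well on either reading:

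- Applied to post-test scores, it leaves the baseline out.
- Applied to change scores, it forces a slope of 1 on the baseline. That is less precise than post-test scores alone whenever r is below 0.5.

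Simple randomisation does nothing to balance baseline HC-PAIRS, so a chance gap between groups can feed into the estimate. At stake are the width of the interval around the primary difference and the chance of detecting 4.5 points. The protocol's own limitations section worries about type II error from a small final sample.

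**Working it through.** **Inputs from the Sample size section:** difference 4.5, SD 9, two-sided alpha 0.05, power 80%, 63 per group, dropout 20%. **Assumed, because not given:** the pre-post correlation r (shown at 0.3, 0.5 and 0.7), and equal SDs before and after.

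**1. The plan's figure.** n = 2 × (1.96 + 0.842)² × (9/4.5)² = 62.8, so 63 per group. It reproduces exactly as a plain two-sample comparison with no dropout inflation and no baseline term. Exact power (noncentral t) at 63 per group is 79.5%. If 63 were the number recruited, 20% dropout would leave 63 × 0.8 = 50.4, or about 50 per group, with 69.7% power.

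**2. SD that each analysis works with.** Let σ be the SD of scores.

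- Post-test t test: σ
- Change-score t test: σ√(2(1−r))
- ANCOVA: σ√(1−r²)

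If 9 is the SD of scores, σ = 9. The ANCOVA SD is 8.59, 7.79 or 6.43 at r = 0.3, 0.5 or 0.7. If 9 is the SD of change, σ = 9/√(2(1−r)). The ANCOVA SD becomes 9√((1+r)/2) = 7.26, 7.79 or 8.30.

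**3. Power for 4.5 points** (noncentral t, standardised effect = 4.5 / SD from step 2):

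| Meaning of SD 9 | Analysis | 63 per group, r = 0.3 / 0.5 / 0.7 | 50 per group, r = 0.3 / 0.5 / 0.7 |
|---|---|---|---|
| Scores | t test, post-test | 79.5% at any r | 70% at any r |
| Scores | t test, change | 65 / 80 / 95% | 55 / 70 / 89% |
| Scores | ANCOVA | 83 / 90 / 97% | 74 / 82 / 93% |
| Change | t test, change | 79.5% at any r | 70% at any r |
| Change | ANCOVA | 93 / 90 / 86% | 87 / 82 / 77% |

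ANCOVA is ahead of the t tests in every column shown. The direction with r reverses between the two meanings of 9.

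**4. Interval width** (9 as SD of scores, 63 per group). The standard error is 9√(2/63) = 1.60, so the half-width is 1.96 × 1.60 = 3.1 points. At r = 0.6 ANCOVA multiplies this by √(1−0.36) = 0.8, giving 2.5 points.

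**5. Can ANCOVA offset a fall from 63 to 50 per group?** The variance must shrink by 50/63 = 0.794.

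- 9 as SD of scores: 1−r² ≤ 0.794, so r must be about 0.46 or more.
- 9 as SD of change: (1+r)/2 ≤ 0.794, so r must be slightly below 0.6 or less.

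**6. Chance imbalance** (9 as SD of baseline scores, 63 per group). The standard error of the baseline difference is again 1.60. A gap above 2 points in either direction has z = 2/1.60 = 1.25 and occurs in about 21% of trials. At r = 0.5 a 2-point gap shifts the post-test comparison by 0.5 × 2 = 1 point in one direction and the change-score comparison by (1−0.5) × 2 = 1 point in the other. ANCOVA removes it in expectation.

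**The case against.** The strongest reply is that nothing stated is invalid. Under randomisation an unadjusted t test is unbiased over repeated allocations and holds its type I error, so the issue is efficiency alone. The article is also condensed: a fuller analysis plan may name an adjusted model, and the Data analysis sentence neither mentions HC-PAIRS nor excludes one. Both points are fair and limit the weight of this comment. They do not remove it, because the one parametric test that the article commits to is unadjusted.

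Three stronger readings are tempting, and the documents do not support them.

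- **That the plan discards the baseline.** The text does not say which scores are compared. The target is worded as a variation in HC-PAIRS, which may well mean change, and a change score does use the baseline, imperfectly.
- **That ANCOVA would recover the power lost to dropout.** This depends on an unstated r and an unstated meaning of the SD. At r = 0.3 with 9 as the SD of scores, 50 per group gives only 74%. At r = 0.7 with 9 as the SD of change, it gives only 77%.
- **That there is a dropout shortfall at all.** The figure of 63 is called a minimum. It may be the number to be evaluated, with more recruited: 63/0.8 = 78.75, or 79 per group. The article does not say.

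**Conclusion.** The point holds as a free improvement to a stated method. The named t test is less efficient than the collected data allow, whichever scores it is applied to. At 63 per group, moving to ANCOVA from the t test on the scale with SD 9 raises power from 79.5% to about 83–97% if 9 is the SD of scores, or to about 86–93% if it is the SD of change, over r from 0.3 to 0.7. This gain needs no assumption about dropout. It rests on an assumed r, equal pre and post SDs and a roughly linear relation between the two scores. If only 50 per group complete, ANCOVA could bring power back to about 80%, but only within the ranges of r derived above. It improves precision; it does not deal with missing post-tests as a source of bias.

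**What to change.** In the Data analysis section, state that the primary analysis is a linear model of post-test HC-PAIRS with group and baseline HC-PAIRS as terms, and report the adjusted mean difference with its 95% confidence interval against the 4.5-point threshold. Use the same model for each FABQ subscale and for the pain neurophysiology score, each with its own baseline. Keep the t test as a sensitivity analysis and say whether it compares post-test or change scores.

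In the Sample size section, state whether the SD of 9 refers to scores or to change, and whether 63 per group is the number recruited or evaluated. If it is the number evaluated, give the inflated recruitment target.

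The cost is a few sentences. The baseline scores are already collected and SPSS, the planned software, fits the model directly. The change should be made before outcome data are seen by group.

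### The observed distribution decides whether HC-PAIRS is compared by t test or by a rank test, so the primary effect measure is not fixed in advance and may not be the mean difference used for sizing

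*Protocol article*

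**What the plan says.** The Sample size section of the protocol article defines the quantity of interest on the mean scale. It states that "a standard deviation of 9 will be considered for the calculation of statistical power" and that "A variation in the HC-PAIRS score of 4.5 (half the standard deviation) will be considered clinically significant". With "Accepting an alpha risk of 0.05 and a statistical power of 80% to reject the null hypothesis, using a bilateral test", it concludes that "the minimum number of participants will be 63 HP in each group". A dropout rate of 20% is assumed, without saying whether 63 is the number before or after dropout.

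The Data analysis section (QUAN) names the default: "The t-Student test will be used for the comparison between the continuous variables". It then makes that default conditional: "A non-parametric test will be used for the bivariate analysis if a normal distribution cannot be assumed". In the descriptive analysis, mean and SD give way to median and interquartile range on the same condition. No outcome is exempted, so the rule covers HC-PAIRS, named as the primary outcome measure.

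The Data collection section says that the variables are measured both before and after the two-week intervention, so a baseline value exists for every questionnaire.

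**The concern.** The two sections do not fit together. One sizes the trial on a difference in mean HC-PAIRS score and calls 4.5 points clinically significant. The other lets the data decide whether the test of that outcome concerns means at all. A rank test such as Mann-Whitney asks whether scores in one arm tend to be higher than in the other. It does not itself test or estimate a mean difference, except under added assumptions such as a pure shift between same-shaped distributions.

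At stake is whether the main result will be a number of HC-PAIRS points that can be read beside the 4.5-point target. Under the stated rule, that is known only once the data have been seen. The problem lies in a rule the article states, not in a detail it leaves out: an analysis plan that follows the sentence would inherit it.

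**Working it through.** **1. The plan's own figure.** Inputs from Sample size: difference 4.5, SD 9, two-sided alpha 0.05, power 80%.

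n per group = 2 × (1.960 + 0.842)² × 9² / 4.5² = 2 × 7.849 × 4 = 62.8, so 63.

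This matches the stated 63. (The noncentral t version gives 63.8.) The calculation is one for two means.

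**2. Number analysed.** If 63 is the number enrolled, 63 × 0.8 = 50.4, so about 50 per group remain and power is 70.5% (normal approximation). If 63 is the number analysed, 63 / 0.8 = 78.75, so 79 must be enrolled. The figure of 50 is a derived reading; both 50 and 63 were checked.

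**3. How the rule behaves.** The article gives no trigger, no named rank test and no HC-PAIRS distribution. The following are assumptions: the switch occurs if Shapiro-Wilk gives p < 0.05 in either arm, the rank test is Mann-Whitney, scores are rounded to integers with SD 9, and the effect is a pure shift of 0 or 4.5 points. There were 4,000 simulated trials per scenario (simulation standard error about 0.3 to 0.8 percentage points). Results at 63 per group, in %:

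| Shape in both arms | Switch rate (no effect) | Type I, t test | Type I, with switch | Power, t test | Power, with switch |
|---|---|---|---|---|---|
| Normal | 11.2 | 4.8 | 4.9 | 79.7 | 79.7 |
| Moderate skew (gamma, shape 4) | 96.9 | 4.7 | 5.1 | 80.2 | 85.8 |
| Strong skew (gamma, shape 1.5) | 100 | 4.7 | 4.8 | 80.1 | 93.6 |
| Negative skew (beta) | 99.7 | 4.7 | 4.3 | 79.6 | 82.9 |
| Heavy tails (t, 5 df) | 67.1 | 4.9 | 4.6 | 80.1 | 86.0 |
| Uniform | 99.0 | 4.5 | 4.6 | 78.9 | 74.5 |

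At 50 per group the pattern is the same. The t test's type I error is 4.8–5.5% and its power 69–70%; with the switch, power is 69% (normal), 87% (strong skew) and 65% (uniform).

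**4. Does the choice of test matter for the result?** With a true 4.5-point shift, the t test and Mann-Whitney gave different significance verdicts in 5–7% of normal trials and in up to 18% of strongly skewed ones.

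**5. Does the hypothesis change?** With equal means but one arm normal and the other strongly skewed, the switched procedure rejected in 9.4% (50 per group) and 10.7% (63 per group), against 4.8% and 5.7% for the t test. The rank test is responding to the difference in shape. This illustrates that the target changes; nothing in the article suggests that the arms will differ in this way.

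**6. What baseline adjustment offers.** For an assumed pre-post correlation r, the residual SD is 9 × √(1 − r²). At 63 per group the standard error is that SD × √(2/63):

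- r = 0.4: SD 8.25, SE 1.470, 4.5/1.470 = 3.06, power = Φ(3.06 − 1.96) = 86%.
- r = 0.6: SD 7.20, SE 1.283, 4.5/1.283 = 3.51, power = Φ(3.51 − 1.96) = 94%.

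Simulation gave 85–87% and 92–94%. The article states no correlation.

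**The case against.** The strongest reply is that a t test with a non-parametric fallback is a conventional summary in a condensed article. The trigger, the named test and the accompanying estimate are details that an analysis plan commonly supplies. That stands, and the absence of those details is not held against the article here. It does not answer the point that the stated rule lets the primary test depend on the data and does not exempt the primary outcome.

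Several stronger readings are tempting and are not supported:

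- A reader might infer that the switch brings no benefit at this sample size. It brings none for type I error, but under a pure shift it raised power in four of the six shapes in the table, for example from 80% to 94% under strong skew. It lowered power only for uniform scores. The article gives no HC-PAIRS distribution, so such a gain is neither shown nor excluded.
- A reader might infer that choosing the test after a normality check inflates type I error. With same-shaped arms it did not: 4.3–5.5% throughout.
- A reader might infer that the switch is what prevents baseline adjustment. The default t test as described does not adjust either, and rank methods can be applied to change scores or extended to covariates. For the same reason, the higher power of a baseline-adjusted analysis is an argument for adjustment, not evidence against ranks. At 50 per group and an assumed correlation of 0.6, power is 68% for the rank test, 70% for the unadjusted t test and 87% for ANCOVA, so nearly all of the gap is due to adjustment.
- A reader might infer that a rank analysis could never be expressed in HC-PAIRS points. A Hodges-Lehmann shift could accompany it, and mean differences could still be reported. The median and interquartile range belong to the descriptive analysis only, and no rule in the article judges the final estimate against 4.5. What remains is that the article does not commit to any such estimate.

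**Conclusion.** The point holds in a limited form. The Data analysis section leaves the primary test, and with it the effect measure, to be settled by the observed distribution. If the switch occurs, the primary test no longer targets the mean difference behind the 4.5-point, 63-per-group calculation. The switch is unnecessary for validity at 50 to 63 per group, and it is harmless to type I error when the arms have the same shape.

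How often it would occur is uncertain. The 10–11% for normal and 91–100% for skewed scores rest on the assumed Shapiro-Wilk trigger and assumed distributions; a graphical judgement could behave differently. The conclusion that the effect measure is not fixed does not depend on those rates. This is a modest defect with a nearly free repair. It does not make the planned test invalid, and the stated sample size is unaffected.

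**What to change.** Exempt the trial outcomes from the conditional rule. State that HC-PAIRS, and likewise FABQ and NPP, will be compared between groups by a mean difference with 95% CI adjusted for the pre-test score (ANCOVA), whatever the distribution, with robust or bootstrap standard errors if scores are skewed. Name a rank-based test as sensitivity analysis. Keep the choice between mean/SD and median/IQR for the descriptive tables.

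The cost is one added sentence. No further data are needed, because the pre-test is already collected, and the 63 per group can stay. There is one real trade-off: if scores turn out strongly skewed, a rank test might have had more power than the mean comparison. Against that, adjustment is expected to gain power over the planned unadjusted t test, by the amounts in the working if the correlation lies between 0.4 and 0.6.
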